**Secondary end points**					
	Deaths (from cardiovascular causes)	Intervention will reduce cardiovascular-related deaths	Cardiovascular mortality (binary)	End of trial	Chi-square test
	6-minute walk test	Improvement in distance walked in 6-minutes	Distance in meters (continuous)	Baseline and end of trial	✓
	NYHA^b^ functional class	Improvement in dyspnea	Functional class 1, 2, 3, and 4 (ordinal)	Baseline and end of trial	✓
	KCCQ^c^	Improvement in symptoms of heart failure	Questionnaire (ordinal)	Baseline and end of trial	✓
	Trans-esophageal echo	Improvement in ejection fraction	Ejection fraction measured in percentage (%; continuous)	Baseline and end of trial	✓
	NT-pro^d^ and BNP^e^ levels	Reduction in levels	Concentration units (pg/mL; continuous)	Baseline and end of trial	✓

^a^Not applicable.

^b^NYHA: New York Heart Association.

^c^KCCQ: Kansas City Cardiomyopathy Questionnaire.

^d^NT-pro: N-terminal prohormone.

^e^BNP: brain natriuretic peptide.

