## Abstract

**Background:**

Chronic heart failure has high morbidity and mortality, with approximately half of the patients dying within 5 years of diagnosis. Recent additions to the armamentarium of anti–heart failure therapies include angiotensin receptor-neprilysin inhibitors (ARNIs) and sodium/glucose cotransporter 2 inhibitors (SGLT2is). Both classes have demonstrated mortality and morbidity benefits. Although these new therapies have morbidity and mortality benefits, it is not known whether rapid initiation is beneficial when compared with the conventional, slower-stepped approach. Many clinicians have been taught that starting with low-dose therapies and gradually increasing the dose is a safe way of intensifying treatment regimens. Pharmacologically, it is rational to use a combination of drugs that target multiple pathological mechanisms, as there is potential synergism and better therapeutic outcomes. Theoretically, the quicker the right combinations are used, the more likely the beneficial effects will be experienced. However, rapid up-titration must be balanced with patient safety and tolerability.

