#### Statistical Methods

Patient demographic and clinical profiles will be described using the statistical software SAS (version 9.4; SAS Institute). Continuous variables will be expressed as an absolute number, with associated percentage, mean, SD, median, and range where applicable. Clinical assessment of response to heart failure therapy will be performed using the Kansas City Cardiomyopathy Questionnaire, New York Heart Association functional classification, 6-minute walk distance, and hospital admission for heart failure. Objective measures of therapy response will be ascertained by serial N-terminal prohormone of brain natriuretic peptide levels and 2D echocardiography. Echocardiographic features of response to therapy will be characterized according to left ventricular ejection fraction as determined by the Simpson biplane method, global longitudinal strain, and speckle tracking.

Associations between outcomes and indicator variables will be explored through logistic regression. Where appropriate, indicator variables and specific outcomes will be investigated individually through a univariate analysis. Where significant, variables will be entered into and controlled for in a Cox-proportional hazards regression model. Adjustment for confounding will be performed by a competing risks analysis and propensity score matching (Table 1).

**Table 1 table1:** Statistical methods.

Outcome measures		Hypothesis	Measure	Time points	Analysis methods
**Primary** **end points**		The intervention will reduce the outcome from baseline to 5 years.	—^a^	—	—
	All-cause mortality	Rapid sequencing of anti–heart failure therapy will reduce all-cause mortality.	All-cause mortality (binary)	End of trial	Cox proportional hazards regression
	Hospitalization	Rapid sequencing of anti–heart failure therapy will reduce all-cause mortality.	Hospitalized for heart failure (binary)	End of trial	Cox proportional hazards regression

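### Table 1 tests cardiovascular death with a chi-square that cannot account for dropout, and gives the serial NT-proBNP and echocardiography readings no stated role

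*Protocol article*

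**What the plan says.** Table 1 gives cardiovascular death the measure "Cardiovascular mortality (binary", the time point end of trial, and the method "Chi-square test". The all-cause mortality and heart failure hospitalization rows are also labelled binary at end of trial, but their method is Cox proportional hazards regression.

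For the 6-minute walk, NYHA class, KCCQ, ejection fraction and NT-proBNP, Table 1 gives the time points "Baseline and end of trial" and only a tick mark as method. The text of Statistical Methods says instead: "Objective measures of therapy response will be ascertained by serial N-terminal prohormone of brain natriuretic peptide levels and 2D echocardiography".

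The same section names a competing risks analysis, but for another purpose: "Adjustment for confounding will be performed by a competing risks analysis and propensity score matching". It is not tied to cardiovascular death.

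Other relevant statements:
- Sample Size assumes 10% dropout per arm.
- Analysis Population keeps withdrawn participants in the analysis.
- Textbox 1 lists adverse drug reactions as a withdrawal criterion.
- The Abstract gives 5 years of follow-up and a contrast of 4 weeks against 6 months to full therapy.

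**The concern.** Two death outcomes in one table are analysed by different methods, and no reason is given. The chi-square needs a yes or no for every patient at the end of trial. A patient lost in year 2 has no such status, so must be coded as no event or left out. Neither choice uses the follow-up that patient did contribute. If rapid initiation leads to more withdrawals for adverse reactions, and the Discussion itself mentions hypotension and other adverse effects, the coding choice can shift the comparison between arms.

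For function and biomarkers, the only post-baseline reading in Table 1 comes long after both arms are due to be on the same drugs, and some patients will have died by then. The earlier NT-proBNP and echocardiography readings, which lie closest to the contrast, are promised in the text but have no place in the table.

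**Working it through.** **The plan's own figure.** The document gives no calculation for secondary outcomes. Its event target reproduces: 4 × (1.960 + 0.842)² / (ln 0.70)² = 247 events (Schoenfeld), against 248 stated. Power at 248 events is Φ(√248/2 × 0.357 − 1.96) = Φ(0.848) = 80.2%. The same formula is used below for the Cox analysis of cardiovascular death.

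**Inputs.** From the documents: 292 per arm, 5 years, 10% dropout per arm. Assumed, because the documents give no figure: 5-year control mortality of 25 to 50%, 80% of deaths cardiovascular, cardiovascular hazard ratio 0.70, constant hazards. The Abstract says "approximately half of the patients dying within 5 years of diagnosis", but this is a background statement and not a design assumption, so 50% serves as the top of the range.

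**Step 1: equal dropout of 10%.** With cardiovascular hazard h1, other-death hazard h2, loss hazard c and H = h1 + h2 + c, the observed proportion with lost patients counted as no event is h1/H × (1 − exp(−5H)). At 50% mortality, h1 = 0.8 × 0.1386 = 0.1109, h2 = 0.0277 and c = −ln(0.9)/5 = 0.0211. This gives 38.2% in the control arm and 28.8% in the rapid arm, or 292 × (0.382 + 0.288) ≈ 195 events.

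| Control mortality | Risk ratio, full follow-up | Risk ratio, observed | Chi-square power | Cox power |
|---|---|---|---|---|
| 25% | 0.724 | 0.723 | 40.5% | 41.5% |
| 35% | 0.735 | 0.734 | 52.9% | 54.5% |
| 50% | 0.754 | 0.753 | 67.5% | 70.3% |

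The risk ratio barely moves, and the power loss is 1 to 3 points.

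**Step 2: unequal dropout, no true effect.** Assume 5% against 15% loss, with lost patients counted as no event. At 50% mortality the observed proportions are 39.1% and 37.3%. The difference is 0.46 standard errors, and type I error is 1 − Φ(1.96 − 0.46) + Φ(−1.96 − 0.46) = 7.4%. At 35% mortality it is 6.6%, and at 25% it is 6.1%. The spurious risk ratio is about 0.95, or 1.05 if the arms are swapped.

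**Step 3: the direction depends on the coding.** Take identical 30% cardiovascular mortality, no other deaths, and assumed loss of 10% against 20%.
- Lost counted as no event: 28.6% against 27.1%, ratio 0.95.
- Lost left out: the event-free patients still under observation are 0.7 × 0.9 = 0.63 and 0.7 × 0.8 = 0.56. The proportions become 0.286/(0.286 + 0.63) = 31.2% and 0.271/(0.271 + 0.56) = 32.6%, ratio 1.04.

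The document does not say which coding applies.

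**Step 4: function and biomarkers at 5 years.** The slower arm is due to be on full therapy by 6 months, so the reading falls 5 − 0.5 = 4.5 years later. Control patients able to supply a value number 292 × 0.9 × 0.75 = 197 at 25% mortality and 292 × 0.9 × 0.50 = 131 (45% of 292) at 50%.

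A simulation of 1,000,000 draws estimated the effect of comparing survivors only. It assumed a mortality effect of 0.70, no effect on function, a frailty that raises the log hazard by 0.5 or 1.0 per SD, and a correlation of 0.3 to 0.7 between frailty and function. The rapid arm then had 155 to 214 values, and the spurious difference was 0.01 to 0.07 SD against the rapid arm.

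**The case against.** The strongest defence is that the plan expects equal dropout, and Step 1 shows the chi-square then does almost no harm. That stands. Unequal loss is plausible from the withdrawal criterion, but its size is assumed here.

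A reader might infer three stronger points that the documents do not support:
- *Deaths from other causes distort the chi-square.* With complete follow-up they do not: the 5-year proportion is the cumulative incidence, and a patient who died of another cause is rightly counted as not having died of a cardiovascular cause.
- *The chi-square favours the arm that loses more patients.* Step 3 shows that this reverses with the coding rule, which is not stated.
- *Function and biomarkers are analysed only in 5-year survivors.* The article does not say so. How deaths are scored may be set out in an analysis plan that is not shown.

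It can also be said that a summary table in a condensed article does not forbid use of the serial data. That is fair, and the point is therefore that text and table disagree, not that data are thrown away. Finally, moving the main time points to 6 and 12 months and adding walk-test and KCCQ recordings would change the 5-year question. It could also conflict with the Discussion's undertaking that clinicians will do nothing beyond routine clinic work. That objection stands, and no such change is proposed.

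**Conclusion.** The point holds in a limited form. The chi-square for cardiovascular death is a weaker choice than the Cox regression used in the neighbouring rows. It costs about 1 to 3 power points under equal 10% dropout. It may be biased under unequal dropout, with type I error of about 6 to 7% at an assumed 5% against 15% loss counted as no event. These figures rest on the assumed mortality range, cardiovascular share and constant hazards given above.

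The mismatch between "serial N-terminal prohormone of brain natriuretic peptide levels and 2D echocardiography" in the text and "Baseline and end of trial" in Table 1 is a plain inconsistency. A patient who has died cannot supply a 5-year value, so survivor bias is possible. It is not shown, and was at most 0.07 SD in the scenarios run. All of this concerns secondary outcomes; the primary analysis is untouched.

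**What to change.** 1. In the cardiovascular death row, replace the chi-square with time from randomization to cardiovascular death in a cause-specific Cox model, censoring at loss to follow-up. Show cumulative incidence curves with non-cardiovascular death as a competing event. This gives the competing risks analysis already named in Statistical Methods a proper place. Censoring assumes that loss is unrelated to cardiovascular risk, so losses and their reasons should be reported by arm.
2. Reconcile Statistical Methods with Table 1 by listing the serial NT-proBNP and echocardiography readings already planned and analysing them in a baseline-adjusted repeated-measures model.
3. Keep the 5-year functional and biomarker comparisons, and support them with a rank analysis that places deaths worst.

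The cost is table wording and modest analysis work, with no added visits or measurements. The article says funding and ethics clearance are still to be obtained, so the change can be made before enrolment.

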### Ethical Considerations

This study will be conducted in accordance with the principles laid down by the 18th World Medical Assembly [12]. Study participants’ data will be deidentified of names and surnames and identifying information. An application for ethical approval will be submitted to the Stellenbosch University Research and Ethics Committee. The study will be performed in accordance with local regulations, including local data protection regulations and requisite hospital and Provincial Department of Health Approval. Posttrial access and care will be provided to all study participants, throughout their lifespan.

## Results

We are currently in the process of generating funding. If funding is obtained, we will apply for ethical clearance and requisite permissions.

## Discussion

### Principal Findings

This study aims to determine if rapid sequencing of anti–heart failure drugs with proven morbidity and mortality benefits would be superior to slower titration of these therapies.

We chose a composite end point to reduce the sample size, as a larger sample size would result in greater costs and reduce the feasibility of the study. Given the high mortality and frequent hospitalizations for heart failure, we included both events in the combined primary efficacy endpoint.

Intuitively, it makes sense to ensure that the most efficacious heart failure therapies are initiated as soon as possible. Given that the therapies have varied modes of action, we hypothesize that if they are started together as soon as possible, they would have greater benefits than starting them later. Combination therapies are likely to target different pathophysiological aspects of heart failure and thus improve clinical outcomes. Issues with rapid initiation may potentially include hypotension and other adverse effects. We will guard against hypotensive events by starting with the lowest possible dose and stopping the drug if the patient becomes hemodynamically unstable. Furthermore, study participants are required to be euvolemic before rapid sequencing so that we do not worsen patients’ heart failure and thus limit hemodynamic instability and decompensated heart failure. It is a standard clinical practice to ensure euvolemia before titration of anti–heart failure therapies. Euvolemia is usually achieved by loop diuretics [8].

We chose a relatively young group of patients so that underlying issues such as ischemic heart disease are less probable and would not serve as confounders. Furthermore, this group of patients may benefit from the increased life expectancy as compared with the older group.

The public health sector in South Africa has resource constraints. Often, there are not enough clinicians to adequately manage the patients. Thus, doing trials in this setting is challenging. However, given the proven safety and efficacy of ARNIs, SGLT2is, and MRAs, and their widespread use in high-income countries, we envisage limited problems. Furthermore, making these novel therapies available to a vulnerable population would serve as a motivation for clinicians who work in this setting. The setting is a teaching and training facility, and having exposure to these novel therapies will grow the expertise and skills of health care practitioners. Furthermore, we envisage reducing the complexity of the study by using a pragmatic study design so that we can integrate the trial into routine clinical practice in the department of cardiology. This will reduce the administration burden while also resulting in the collection of safety, efficacy, and tolerability data. We feel that the trial would not add to the administrative burden of the clinicians, as we will not ask them to do any work beyond what they usually do in the clinic. Furthermore, a separate designated individual will collect and analyze the data, so that clinicians will not be burdened with this task and not impinge on their demanding clinical work.

Posttrial access and posttrial care are contentious issues [13]. In this study, we plan to provide both posttrial access and posttrial care because it is, in our opinion, ethically justified. Given that the newer therapies are efficacious, safe, and tolerable, it would be unkind to stop the therapies after the trial is completed, as the study participants would not be able to procure the therapy privately because of their limited financial resources. The provision of posttrial care would also increase the cost of the study, but we will continue to provide posttrial care in our cardiology clinic at no cost to the study participants.

We hope to acquire funding from the manufacturers of ARNIs, SGLT2is, β-blockers, and MRAs, as the data generated from this study have the potential to inform clinical practice guidelines. Given the high costs of doing such trials, we hope companies will assist if they are only providing the drug and not covering the other clinical trial costs like investigator fees, protocol development, manuscript writing, and statistical analysis, and so on. The study has dual objectives of generating of evidence while also providing patients with access to highly efficacious and premium therapies for heart failure.

Given that both study groups will receive the same therapies, we do not pitch drugs head-to-head, as we feel that the combination of drugs with proven mortality and morbidity data would be most likely to have synergistic effects and further reduce morbidity and mortality. This approach is also more likely to generate funding as all companies can contribute to financing the study, not with the risk of their products being negatively affected by head-to-head trials that show one drug being superior to another drug.

We have tried to create a “win-win” situation by generating data to inform clinical practice guidelines and providing access to novel therapies in resource-limited settings. The research can help with master’s and PhD degrees, given the rich dataset generated.

### Limitations

The study is proposed to use one study site in the Western Cape of South Africa, which may not be reflective of the demographics of the South African population. Due to the nature of the study and means of intervention, implementation of a placebo-controlled arm will not be possible but is nonetheless cited as a limitation.

### Conclusions

Recent additions to the armamentarium of anti–heart failure therapies such as ARNIs and SGLT2is have demonstrated morbidity and mortality benefits. Earlier use of such therapy within patients with stable HFrEF may impact patient outcomes. This study will provide important data to support evidence-based medicine and will help inform clinical practice guidelines on the optimal rate of sequencing of anti–heart failure therapies.

## Abbreviations

ARNI: angiotensin receptor-neprilysin inhibitor
HFrEF: heart failure with reduced ejection fraction
MRA: mineralocorticoid receptor antagonist
SGLT2i: sodium/glucose cotransporter 2 inhibitor
